## Abstract

**Background:**

COVID-19 was characterized by the World Health Organization (WHO) as a pandemic in 2020. Papua New Guinea (PNG) has remained on high alert ever since, and its National Control Centre continues to coordinate national preparedness and response measures, guided by its Emergency Preparedness and Response Plan for COVID-19. As part of the WHO and the Global Alliance for Vaccines and Immunization's COVID-19 Vaccines Global Access (COVAX) program, PNG received several shipments of COVID-19 vaccine doses. A nationwide vaccine rollout for COVID-19 was initiated in PNG in May 2021. Despite the availability of vaccines and the capacity of health systems to vaccinate frontline workers and community members, including high-risk groups, there are still critical issues related to vaccine safety, confidence, and acceptance to ensure the effectiveness of the COVID-19 vaccination campaign. Evidence from studies on COVID-19 vaccine acceptance and demand in low- and middle-income countries (LMICs) suggests that sociocultural characteristics of the community and the behaviors of different vaccine stakeholders, including vaccine recipients, vaccine providers, and policymakers, determine the effectiveness of vaccination interventions or strategies.

**Objective:**

This study will examine sociocultural determinants of anticipated acceptance of the COVID-19 vaccine in urban and rural areas of different regions in PNG and health care providers’ views on vaccine acceptance.

**Methods:**

The study design uses a mixed methods approach in PNG’s coastal and highlands regions. The first research activity will use a qualitative methodology with an epistemological foundation based on constructivism. This design elicits and listens to community members’ accounts of ways culture is a rich resource that provides meaning to the COVID-19 pandemic; the design also measures adherence to *niupela pasin* (“new normal” in Tok Pidgin) and vaccination acceptance. The second activity will be a cross-sectional survey to assess the distribution of features of vaccine acceptance, priorities, and practices. The third activity will be in-depth interviews of health care providers actively involved in either COVID-19 clinical management or public health–related pandemic control activities.

**Results:**

The project proposal has been reviewed and approved by the Medical Research Advisory Committee of Papua New Guinea. Qualitative data collection started in December 2022, and the survey will begin in May 2023. The findings will be disseminated to the participating communities later this year, followed by publication.

**Conclusions:**

The proposed research on community views and experiences concerning sociocultural and behavioral features of acceptance of the vaccine will provide a better understanding of communication and education needs for vaccine action for COVID-19 control in PNG and other LMICs. The research also considers the influence of health care providers’ and policy makers’ roles in the awareness and use of the COVID-19 vaccine.

**International Registered Report Identifier (IRRID):**

PRR1-10.2196/44664

## Introduction

### Background

COVID-19 affected almost every country in the Pacific region, including Papua New Guinea (PNG). As of August 2022, a total of 45,133 confirmed COVID-19 cases were reported in PNG, resulting in 668 deaths [1]. However, these numbers may be an underestimate caused by nonoperational information systems in rural areas. Globally, as a pandemic preventive strategy, countries have been using nonpharmaceutical interventions (NPIs), such as enforced use of face masks, hand sanitization, physical distancing, travel restrictions, avoidance of large gatherings, school closures, and partial or complete lockdowns. [2]. The health department in PNG has introduced the *niupela pasin* (“new normal” in Tok Pidgin) policy, referring to the changes in behavior and habits that individuals and communities need to adopt to prevent the spread of the virus [3]. Despite these NPIs and policies, there have been increased new cases and deaths each day throughout the world.

### COVID-19 Vaccines

Vaccines are the most reliable and effective public health intervention to prevent many infectious diseases [4,5]. Other interventions, like developing practical diagnostic tools and therapeutic drugs, also help clinical management and reduce mortality and morbidity. Therefore, developing and producing safe and effective vaccines remains one of the essential tools for ending the COVID-19 pandemic, along with NPIs [6]. In collaboration with global research institutions, the World Health Organization (WHO) and other global agencies accelerated the development process of COVID-19 vaccines while maintaining the highest standards of safety [7]. The WHO emergency use listing approved several vaccines developed on different platforms. The COVID-19 Vaccines Global Access (COVAX) program is a groundbreaking collaboration between the WHO, the United Nations Children’s Fund (UNICEF), the Global Alliance for Vaccines and Immunization (GAVI), and the Coalition for Epidemic Preparedness Innovations (CEPI) to accelerate the development and production of vaccines and equitable access to them for every nation in the world [8]. So far, the COVAX program has provided 71 million vaccine doses to 125 participating countries [9]. Many countries have initiated vaccine rollouts at a national level since 2021. However, with equitable access to and availability of COVID-19 vaccines, the issue of vaccine acceptance and uptake among different high-risk groups, including frontline health workers and the general population, remains critical.

### Research on COVID-19 Vaccine Acceptance

Although vaccines are generally well-received, the fast-tracking of COVID-19 vaccine development procedures and the use of new platforms, such as RNA-based vaccines, has created some doubts about vaccine safety and reduced confidence. Vaccine confidence can be defined as the trust and willingness of individuals and communities to accept and use vaccines, and it is important to measure vaccine confidence to identify and address community concerns about vaccination [10]. In general, vaccine hesitancy undermines vaccine acceptance and demand. The WHO’s Strategic Advisory Group of Experts (SAGE) on immunization defined vaccine hesitancy as a delay in acceptance or refusal of vaccination despite the availability of vaccination services [11,12]. It is crucial to assess the determinants of vaccine acceptance among vaccine recipients to deal with vaccine hesitancy.

Almost all countries in the world prioritized frontline workers for COVID-19 vaccination. However, research suggests that health care workers’ anticipated COVID-19 vaccine acceptance rates vary from low to high [13-15]. A global survey based on 13,426 participants from 19 countries showed that global acceptance of COVID-19 vaccines ranges between 54.8% in Russia to 88.6% in China [16]. In a narrative review of 15 studies, frequently given reasons for refusing the COVID-19 vaccine were related to the fast-tracked vaccine development and vaccine safety and effectiveness [17]. Nevertheless, the WHO has stated that vaccine safety was not compromised by fast-tracking development [7]. With careful evidence-based communication strategies, it is possible to convey the safety of COVID-19 vaccines to the general population.

### Public Health Priority of COVID-19 Vaccines in PNG

PNG is the largest country in the Pacific region. The health system of PNG has been struggling for decades to provide universal access to quality services [18]. Nevertheless, PNG has remained on high alert ever since COVID-19 was characterized by the WHO as a pandemic in 2020, and its National Control Centre (NCC) continues to coordinate national preparedness and response measures guided by its Emergency Preparedness and Response Plan for COVID-19 [19]. As in many low- and middle-countries (LMICs), even PNG, vaccination is the only way of protecting frontline workers and community members during the COVID-19 pandemic. As part of the COVAX program, 588,000 COVID vaccine doses were allocated for PNG. The National Department of Health initiated a nationwide vaccine rollout for COVID-19 on May 4, 2021 [20]. So far, more than 348,938 doses have been administered in 22 provinces of PNG [1].

### Rationale for This Research

Despite the availability of vaccines and the capacity of health systems to vaccinate frontline health care workers and community members, issues related to vaccine safety, confidence, and acceptance remain critical for the effectiveness of the COVID-19 vaccination campaign. Evidence from studies on differing vaccine acceptance in LMICs suggests that sociocultural factors in the community and the behaviors of different vaccine stakeholders, including vaccine recipients, vaccine providers, and policy makers, determine the effectiveness of vaccination interventions or strategies. So far, no literature exists on determinants of COVID-19 vaccine acceptance in the PNG context.

Understanding the local context is critical for an effective vaccination program at the community level. The proposed research on community views and experiences concerning sociocultural and behavioral features of anticipated vaccine acceptance will enable a better understanding of communication and education needs for vaccine action for COVID-19 control in PNG and other LMICs. Our pilot study, which explored views on COVID-19 vaccines among students (n=90) with different cultural backgrounds at the Faculty of Medicine and Health Sciences of Divine Word University, indicated 50% tentative acceptance and highlighted the role of the media in determining vaccine acceptance.

### Objectives

This study will examine sociocultural determinants of anticipated acceptance of the COVID-19 vaccine in urban and rural areas of different regions in PNG. The following are the specific study objectives: (1) understand community members’ accounts of experiences, meaning, and behavior concerning the COVID-19 pandemic, as well as their awareness of and adherence to *niupela pasin* and their perceptions of vaccines based on Melanesian culture, and (2) assess the role of health care providers in determining COVID-19 vaccine acceptance in the coastal and highlands regions, considering their awareness, acceptance and personal use, and vaccine recommendation practices.

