### Study Groups and Sampling

#### Community Members

The criteria for including community members in interviews and the cultural epidemiological survey are being aged between 18 to 65 years and being cognitively able and willing to participate. The study will be conducted in either English or Tok Pidgin and participants should be able to communicate in either of these languages.

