### Vaccine Acceptance Survey

A random sampling strategy will be used to select the participants for this survey. We plan to use either the voters’ list or household listings to randomize the sample at an individual level or use village maps to randomize households to select the eligible participants. This will be achieved in collaboration with the provincial health authority (PHA). However, randomization depends on the availability of these resources. Otherwise, a convenience sample will be selected from the urban and rural areas of the selected study sites, stratified by gender (with a 50% distribution) and age group (18-40 years and 41-65 years). Trained research assistants working in 2 teams will conduct the survey, one interviewing and the other responsible for maintaining the data records. Approximately 360 interviews will be conducted (180 in each of the two regions. We calculated the sample size at a 5% margin of error with a 95% confidence level and a 50% response distribution.

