### Analysis Plan

The primary goal of the study is to clarify descriptive, comparative, and analytic accounts of explanatory models of COVID-19 and how they explain awareness, acceptance, and use of vaccines. Comparative analysis will focus on questions of gender and rural-urban features of the COVID-19 pandemic and determinants of anticipated acceptance or refusal of COVID-19 vaccines.

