### Quantitative Analysis

The epidemiological survey will be conducted on tablets with ODK software. All interviews will be uploaded electronically to Google Spreadsheets (Google Inc). The final data set will be downloaded as Excel spreadsheets. STATA/SE (version 16.1; Stata Corp) will be used for statistical analyses. A descriptive analysis will be conducted to summarize the important results. The sociocultural and demographic characteristics of the participants will be summarized. Illness-related questions, such as perceived causes, distress patterns, and help-seeking behaviors, will be presented and compared between different gender and age groups across study areas. The explanatory variables in this study will be social and cultural features of illness experience, meaning and behavior, and questions of awareness and use of the COVID-19 vaccines for prevention. Inferential analysis using regression models will assess the determinants of COVID-19 vaccine acceptance. Narratives of statistically significant factors will be reviewed to better understand their importance.

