## Results

The project proposal has been reviewed and approved by the Medical Research Advisory Committee of PNG. The permissions required from the provincial health authority to conduct data collection in the selected provinces have been obtained. The research team has recruited participants for in-depth interviews, including key informants in the communities and health facilities. The qualitative data collection started in December 2022, and the preliminary analysis of these data is underway. The insights from the in-depth interviews will be used to further refine the survey instrument by adapting it to the local context. We plan to pretest the survey instrument for validity and proceed with the survey in May 2023. The findings from the interviews and the survey will be disseminated to the participating communities and key stakeholders in a professional dissemination meeting, followed by publication.

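### The stated outcome, anticipated acceptance, does not fit a survey of all adults two years into the rollout, and vaccine use sits among the predictors of acceptance

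*Protocol article*

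**What the plan says.** All references are to the protocol article.

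- **Outcome in the aim.** Objectives: "This study will examine sociocultural determinants of anticipated acceptance of the COVID-19 vaccine in urban and rural areas of different regions in PNG". The Analysis Plan keeps the same term and speaks of "determinants of anticipated acceptance or refusal of COVID-19 vaccines".
- **Outcome in the model.** Quantitative Analysis omits the word anticipated: "Inferential analysis using regression models will assess the determinants of COVID-19 vaccine acceptance". No subset of respondents is named.
- **Predictors.** The same section lists among the explanatory variables "questions of awareness and use of the COVID-19 vaccines for prevention". The Analysis Plan, by contrast, places use next to awareness and acceptance as things to be explained.
- **Who is surveyed.** Community Members sets eligibility as "being aged between 18 to 65 years and being cognitively able and willing to participate", plus the ability to communicate in English or Tok Pidgin. Under Vaccine Acceptance Survey, the fallback convenience sample is stratified by gender and age group. Vaccination status appears in neither place.
- **Timing.** Public Health Priority of COVID-19 Vaccines in PNG dates the start of the rollout to 4 May 2021 and adds: "So far, more than 348,938 doses have been administered in 22 provinces of PNG". Results says: "We plan to pretest the survey instrument for validity and proceed with the survey in May 2023".

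**The concern.** Anticipated acceptance is a natural outcome before a vaccine is offered. Two years into a rollout, a general adult sample will contain people who have already been vaccinated. Their answer to an acceptance question reports past behaviour, or perhaps willingness to have a further dose. It is not the intention that an unvaccinated person reports.

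Two things are at stake. First, the survey is sized on a single proportion, and the value and meaning of that proportion depend on how the vaccinated are classified. This is a matter of definition, so a larger sample does not reduce it. Second, the regression is meant to identify determinants of acceptance. If the vaccinated count as acceptors and personal vaccine use is also a predictor, part of the outcome is being used to explain itself.

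**Working it through.** **1. The plan's own figure.** Vaccine Acceptance Survey gives about 360 interviews, 180 per region, from a 5% margin, 95% confidence and a 50% response distribution.

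- n = 1.96² × 0.5 × 0.5 / 0.05² = 384.1, rounded up to 385. The stated 360 is not reproduced.
- With n = 360 the margin is 1.96 × √(0.25/360) = 5.16 points.

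This shortfall is a separate matter. It is shown only because the 5-point margin is the yardstick below.

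**2. Time since rollout.** From 4 May 2021 to the start of May 2023 is 1.99 years.

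**3. Effect of classification on the proportion.** Let v be the vaccinated share of respondents and p the acceptance among the unvaccinated. Counting the vaccinated as acceptors gives v + (1 − v)p. Relative to the unvaccinated alone, the shift is v(1 − p).

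- p = 50%, taken from the article: it is the response distribution used for the sample size, and the student pilot in Rationale for This Research also found 50% tentative acceptance.
- v is **assumed**, because the article gives no coverage for the study districts.

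| v (assumed) | Vaccinated of 360 | Unvaccinated left | Proportion, vaccinated counted as acceptors | Shift from 50% | Margin in unvaccinated only |
|---|---|---|---|---|---|
| 5% | 18 | 342 | 52.5% | 2.5 points | 5.3 points |
| 10% | 36 | 324 | 55% | 5 points | 5.4 points |
| 20% | 72 | 288 | 60% | 10 points | 5.8 points |

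The shift equals the planned 5-point margin when v = 5/50 = 10%. It equals the 5.16-point margin that 360 interviews give when v = 5.16/50 = 10.3%.

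**4. How far the article bounds v.** Only loosely. Study Sites gives 579,825 people for one Highlands province and puts the whole Highlands region at 23% of the country (2011 census). The national population is therefore at least 579,825/0.23, about 2.52 million. The quoted dose count is then at most about 348,938/2,520,978 = 0.14 doses per head. These are doses, not persons; they cover all ages and the whole country; and the count is stated as a minimum reached before the survey. Adult coverage at the sites could lie on either side, though the 20% row may be high.

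**5. Predictor and outcome.** Suppose the use questions record personal uptake. Take the 10% row.

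- *Vaccinated counted as acceptors, all 360 analysed.* The vaccinated split 36 accepting to 0 not accepting; the unvaccinated split 162 to 162. Use predicts acceptance without exception in its group. In a logistic model, for instance, the odds ratio for use has no finite estimate.
- *Unvaccinated only.* Use takes one value throughout and carries no information.
- *Vaccinated asked about further doses.* The model pools answers to two different questions.

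None of these gives a regression coefficient for personal use that can be read as a determinant of anticipated acceptance.

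**The case against.** The strongest reply is that this is detail an article leaves elsewhere. The questionnaire is not shown. Data Management and Analysis Plan says it will be developed further after the qualitative phase, and Results says it will be refined and pretested. It may well separate uptake from intention. That stands as far as item wording and coding rules go, and their absence is not the point here. What remains is a mismatch in what the article does print: its outcome, its survey population and its predictor list.

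A reader might also infer more than the text supports:

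- *That the authors treat intention and uptake as one thing.* They do not. The Analysis Plan lists acceptance and use as separate items, and Expected Outcomes names anticipated and actual acceptance side by side. Anticipated acceptance or refusal is simply the two directions of one variable.
- *That the plan pools the vaccinated with the willing.* No section says so. The stated analysis allows pooling and does not prescribe it.
- *That the shift exceeds the planned margin from 10% vaccinated.* That needs acceptance below 50% among the unvaccinated, a value the article does not give. At 50% the shift equals the 5-point margin and falls just short of the 5.16 points that 360 interviews deliver.
- *That associations would reflect mandates or occupation and not culture.* The article gives no information on what drove uptake in PNG, so this cannot be argued from it.

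It is also fair to say that the aim covers a three-part mixed methods study, and that the choice among outcomes is partly a preference. The survey is nevertheless sized on a proportion, and its regression concerns acceptance, so the outcome has to be defined for everyone enrolled.

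**Conclusion.** The point holds as a mismatch between outcome, population and predictors, and it should be corrected before the survey starts. Anticipated acceptance is the named outcome, the sample is open to vaccinated adults two years after rollout, and the regression outcome loses the word anticipated while vaccine use enters as a predictor.

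The size cannot be fixed from the article. With 50% acceptance among the unvaccinated and an assumed 5% to 20% vaccinated, the classification of the vaccinated moves the proportion by 2.5 to 10 points, reaching the planned margin at about 10%. The overlap of predictor and outcome is conditional on the use questions meaning personal uptake, which the article does not settle.

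**What to change.** - Record vaccination status in the survey, and report three levels: already vaccinated; unvaccinated and willing; unvaccinated and unwilling.
- Fit two separately labelled models: ever-accepted (vaccinated or willing) in all respondents, and anticipated acceptance in the unvaccinated.
- Leave personal vaccine use out of the predictors in both. Awareness items can stay.
- Use the same outcome terms in Objectives, Analysis Plan and Quantitative Analysis.

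The cost is small while the instrument is still being refined: a status item, if the planned use questions do not already supply it, and some wording. There are two downsides. The unvaccinated-only model has fewer than 360 people: 342 to 288 under the assumed range, with margins of about 5.3 to 5.8 points. It also conditions on two years without vaccination and leaves out everyone who has already accepted, so it cannot stand alone as an account of acceptance in the community and should be read beside the ever-accepted model.

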## Methods

### Study Design

The research project will use a mixed methods design. The first research component will use a qualitative methodology with an epistemological foundation that is based on constructivism and embraces meaningful reality as it is socially constructed [21]. This design elicits and listens to community members’ accounts of ways culture is a rich source of meaning in the COVID-19 pandemic, their adherence to *niupela pasin*, and their vaccination acceptance. In the context of health, adherence to the new normal is an indicator of the behavior of communities toward their health and is important for understanding these communities. This design will proceed with individual, in-depth, semistructured interviews with community members, community opinion leaders, and church leaders.

The second component, a cross-sectional survey, will use data collected from ethnographic key informant interviews to develop an instrument with open-ended and closed questions. The survey design adapts the WHO immunization and vaccine-related implementation research advisory committee’s vaccine stakeholder framework to assess the awareness, priorities, and practices of community members. This design includes an integrated quantitative and qualitative methods approach, and the data collected will indicate the distribution of key features of vaccine acceptance and demand [22].

The third component, semistructured interviews with health care providers actively involved in either COVID-19 clinical management or public health–related pandemic control activities, will determine vaccine acceptance factors. This component will focus on assessing health care providers’ views on personal vaccine acceptance and their role in facilitating community vaccination.

